### 3. STUDY DESIGN

The original 2019 RISING-trial (RISING trial A) was designed as an open label, randomized, non-inferiority, phase III trial with 1:1 allocation for 130 patients. In this trial 13 patients were included in the experimental arm and 16 patients were included in the control arm. The updated 2023 RISinG trial (RISING trial B) is designed as a phase II, multi-center, clinical trial with a historic control group. The additional recruitment period of this phase will be approximately 30 months with an active follow-up time of 12 months.

The 13 patients of the RISING trial A will be supplemented until a total of 66 patients is reached. These patients fulfilling the inclusion criteria will get the following treatment:

- Hypofractionated radiotherapy with SIB in 2 weeks  
4 fractions of 7.5 Gy SIB to the GTV  
And 4 fractions of 5.5 Gy to the CTV (GTV + 5mm margin).

We will compare the survival of this group with a retrospective control group of patients, subtracted from the retro-RISinG registry study, a multi-center retrospective nation-wide population based cohort study, in which details of patient-, tumor- and treatment-related data of all patients with a recurrence of a primary brain tumor since January 2002 up to December 2022 in the Netherlands will be collected. We will select 99 matched patients in total with the following treatment:

- Moderately hypofractionated radiotherapy in 2-3 weeks  
10 fractions of 3.5 Gy to the CTV (GTV + 5 mm margin)

An overview of the target volume definitions and dose prescriptions is presented in table A3 in section 1.8 of the Appendix.

This control group will be matched to the patients in the experimental arm on an individual level for:

1. Age;
2. Gender;
3. WHO-grade primary tumor;
4. Time interval in between first radiation and re-irradiation;
5. MGMT-status.

[figure not shown]

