### 4.4 Sample size calculation

The sample size required to achieve a power of  $1-\beta = 0.80$  for the one-sided chi-square test at level  $\alpha = 0.05$  when the hazard ratio is actually 0.90, and a distribution of 40% in the intervention group and 60% in the control group, amounts to 165 subjects: 99 in the control group and 66 in the treatment group [30]. The non-inferiority ratio is 1.4. Unfortunately, there are no historical randomized placebo-controlled trials for arm 2 to use to formulate a margin, therefore we collect this data now as well for matched patients. This ratio is based on clinical judgment of the calculated survival fractions at the proposed non-inferiority margins and published survival data [21].

To clarify the meaning of this non-inferiority margin in practice, the non-inferiority margin specific survival fraction at median survival time could be calculated. This non-inferiority margin means in practice that at least 76% of the patients surviving at the median survival

time of the control group would have survived when treated with the experimental treatment. In other words, at least 38 percent of the patients in the intervention group reach the median survival time instead of 50 percent in the control group.

Expected event rate at the minimal follow-up time of 12 months is 0.7 based on the literature [21, 31]. However, a part of the study population may have a longer follow-up period of even up to 3.5 years. It is anticipated that the proportion of subjects observed with the event during the total study period is 0.8. These results assume that the hazard ratio is constant throughout the study and that Cox proportional hazards regression or the non-inferiority log rank test is used to analyze the data. To compensate for any drop-outs or slight deviation from the assumptions made, the total sample size should be 130 patients (10% added to the calculated sample size).

A point of discussion is that we anticipated that the hazard ratio is actually 0.90, however we can in fact not know the actual hazard ratio. It is justified to assume a hazard ratio below 1.0 when hypothesizing that the tumor will be treated slightly better by a higher dose per fraction.

**Table 1. Number of patients to include to achieve a power of 0.80 with a non-inferiority ratio of 1.4 at a decrease rate of 0.80 for different alfa-levels and actual hazard ratios.**

| Alfa/HR | 0.8 | 0.9 | 1.0 |

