|----------------|------------|------------|------------|
| 0.05    | 99         | 159        | 274        |
| 0.10    | 72         | 116        | 200        |

The trial is primarily designed to show non-inferiority, in addition superiority will be tested. If the actual hazard ratio is lower, the patient number will be sufficient to detect superiority (Table 2).

**Table 2. Number of patients to include to achieve a power of 0.80 at a decrease rate of 0.80 for different alfa-levels and actual hazard ratios for superiority analysis.**

| Alfa/HR | 0.4 | 0.5 | 0.6 | 0.7 | 0.8 |
|----------------|------------|------------|------------|------------|------------|
| 0.025   | 47         | 82         | 151        | 308        | 787        |
| 0.05    | 37         | 65         | 119        | 243        | 621        |
| 0.10    | 27         | 47         | 87         | 178        | 453        |

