##### 8.1.1.1. OS

The hazard rate for the experimental versus the retrospective control group and its two-sided 80 and 95% CIs will be estimated using a Cox proportional hazards model. We will adjust for confounding using propensity scores.. Omission of 4 fractions as non-inferior to 10 fractions of radiotherapy if the higher 90% CI of the hazard ratio (HR) of 4 fractions versus 10 fractions was not above 1.4.

Only when non-inferiority has been demonstrated, we will test for superiority of the experimental treatment in a hierarchical fashion, using Kaplan-Meier method and two-sided log-rank test at a significance level  $\alpha = 10\%$  in ITT analysis.

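### Section 4.4 calls the patient number sufficient for superiority without giving a threshold, but 165 patients give 80% power only at a hazard ratio of about 0.64 or lower, and Tables 1 and 2 are on a 1:1 basis

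*Protocol*

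**What the plan says.** Section 4.4 sizes the trial for non-inferiority with margin 1.4, one-sided alpha 0.05, 80% power and a true hazard ratio of 0.90. It uses "a distribution of 40% in the intervention group and 60% in the control group", and the result "amounts to 165 subjects: 99 in the control group and 66 in the treatment group". The anticipated effect appears once more in the same section: "we anticipated that the hazard ratio is actually 0.90". The section expects a proportion of 0.8 of the subjects to have died by the end of the study.

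After Table 1, section 4.4 turns to superiority: "If the actual hazard ratio is lower, the patient number will be sufficient to detect superiority (Table 2". Table 2 follows directly, with the sizes for 80% power:

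| Alpha | HR 0.4 | HR 0.5 | HR 0.6 | HR 0.7 | HR 0.8 |
|---|---|---|---|---|---|
| 0.025 | 47 | 82 | 151 | 308 | 787 |
| 0.05 | 37 | 65 | 119 | 243 | 621 |
| 0.10 | 27 | 47 | 87 | 178 | 453 |

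Neither table states its allocation ratio. Section 8.1.1.1 makes superiority a formal step once non-inferiority is shown ("we will test for superiority of the experimental treatment in a hierarchical fashion"), using a two-sided log-rank test at 10%. Section 3 describes the superseded trial A as a "phase III trial with 1:1 allocation for 130 patients".

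**The concern.** The sentence presents adequate superiority power as a property of the design, yet it sets no limit on the hazard ratio, and the table it cites shows sizes well above 165 at 0.7 and 0.8. The only anticipated value in the section is 0.90, and the stated rationale is a slight improvement in tumour treatment. A reader who takes the sentence at face value would expect the superiority test to be informative for modest benefits. If it is not, a non-significant result after proven non-inferiority could be given more weight than it deserves.

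The two tables also disagree with the text. For one and the same scenario (true hazard ratio 0.90, margin 1.4, alpha 0.05, power 0.80, event proportion 0.8) the text gives 165 and Table 1 gives 159.

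**Working it through.** **Inputs (sections 4.4 and 8.1.1.1).** N = 165, share in the experimental arm p = 0.4, event proportion 0.8, hence 165 × 0.8 = 132 deaths. The margin is 1.4 for non-inferiority and 1 for superiority. Power is 0.80. The superiority test is two-sided 10%, which is one-sided 0.05. Section 4.4 also still carries a total of 130. I use 165 because it is derived there for the current 40:60 split and agrees with the 66 and 99 patients in sections 3 and 4.1.

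**Formula.** N = (z_alpha + z_beta)² / [p(1 − p) × ln(HR/margin)² × 0.8], with one-sided z_alpha. At alpha 0.05, (1.6449 + 0.8416)² = 2.4865² = 6.183.

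**Step 1: the design scenario.** ln(0.9/1.4)² = 0.1952.

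- p = 0.4: 6.183 / (0.24 × 0.1952 × 0.8) = 164.95, which gives the text's 165.
- p = 0.5: 6.183 / (0.25 × 0.1952 × 0.8) = 158.35, which gives Table 1's 159.

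**Step 2: which allocation the tables use.**

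| Row | Printed | p = 0.5 | p = 0.4 |
|---|---|---|---|
| Table 1, alpha 0.05 (HR 0.8, 0.9, 1.0) | 99, 159, 274 | 98.7, 158.4, 273.1 | 102.8, 165.0, 284.4 |
| Table 1, alpha 0.10 | 72, 116, 200 | 72.0, 115.5, 199.1 | 75.0, 120.3, 207.4 |
| Table 2, alpha 0.05 (HR 0.4 to 0.8) | 37, 65, 119, 243, 621 | 36.8, 64.3, 118.5, 243.0, 620.8 | 38.4, 67.0, 123.4, 253.1, 646.7 |

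The 1:1 column gives every printed value in these rows after rounding up; the 40:60 column does not. The other two rows of Table 2 also follow 1:1; the largest gap is 788.15 computed against 787 printed. Reading the Table 2 alphas as two-sided does not fit: at alpha 0.05 it gives 308 and 788 for HR 0.7 and 0.8, not 243 and 621. The tables are therefore 1:1 with one-sided alpha, and the text is 40:60.

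**Step 3: Table 2 against 165.** The one-sided 0.05 row is the one that corresponds to the planned test. It needs 119 at HR 0.6, which 165 covers, and 243 at 0.7 and 621 at 0.8, which 165 does not cover. Another row does not help: at 0.10 the sizes are 178 and 453, and at 0.025 they are 308 and 787.

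**Step 4: power with 165 patients.** Power = Φ(√(132 × 0.24) × |ln HR| − 1.6449), with √31.68 = 5.6285.

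| True HR | 5.6285 × abs(ln HR) | Minus 1.6449 | Power |
|---|---|---|---|
| 0.60 | 2.875 | 1.230 | 89% |
| 0.70 | 2.008 | 0.363 | 64% |
| 0.80 | 1.256 | −0.389 | 35% |
| 0.90 | 0.593 | −1.052 | 15% |

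Power of 80% requires HR = exp(−2.4865/5.6285) = 0.643.

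**Step 5: weight of the allocation point.** Moving from 1:1 to 40:60 multiplies every size by 0.25/0.24 = 1.042. At alpha 0.05 in Table 2, the values at HR 0.4 to 0.6 stay below 165 and those at 0.7 and 0.8 stay above it.

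**The case against.** The strongest defence is that the sentence names no cut-off and sends the reader to a table that openly prints 243 and 621. A reader might infer that the protocol claims adequate power at every hazard ratio below 0.90. That is the natural reference point, but the text does not say it, so the charge has to be a missing threshold and not a false figure. This stands. It does not clear the sentence: read charitably, it states no usable property, and the value it needs appears nowhere.

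Second, superiority does not drive the sample size. It is secondary and tested only after non-inferiority. This also stands. A reader might conclude that the trial is undersized or that 165 is wrong. The documents do not support that, since 165 reproduces at the stated split for the non-inferiority objective.

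Third, the 1:1 basis is inferred by recalculation. The inference is sound, but the effect is about 4% and no Table 2 conclusion at alpha 0.05 turns on it. It should not be put on a level with the power statement.

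Fourth, misreading of a null result is a risk and not something the protocol plans. Section 8.1.1.1 also reports the hazard ratio with confidence intervals, which would show the imprecision.

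Fifth, 0.64 is not exact. It assumes 132 deaths and an unweighted test, while section 8.1.1 applies stabilised inverse-probability weights to overall survival. If, as an assumption, all 165 patients died, the threshold would be exp(−2.4865/√(165 × 0.24)) = 0.67, still below 0.70.

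**Conclusion.** The point holds as a defect in how superiority power is stated. Among the hazard ratios in the protocol's own Table 2, 165 patients suffice at 0.6 and below and fall short at 0.7 and 0.8. By calculation the limit for 80% power is about 0.64, and at the anticipated 0.90 power is about 15%. These figures rest on 132 deaths, a 40:60 split, proportional hazards and an unweighted two-sided 10% log-rank test. Propensity weighting may lower the power further; by how much cannot be worked out from the document.

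The mismatch between Tables 1 and 2 and the text is real but secondary. It amounts to 159 against 165 in the design scenario. The primary sample size, margin, alpha levels and analysis are untouched.

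**What to change.** Replace the sentence on superiority in section 4.4 with wording such as:

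> With 165 patients (99:66), about 132 deaths and an unweighted two-sided 10% log-rank test, superiority has 80% power only if the true hazard ratio is about 0.64 or lower (about 64% power at 0.70, 35% at 0.80 and 15% at 0.90); propensity weighting may lower this further.

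Recompute both tables at 40:60, and state the allocation and the one-sided alpha in their captions. Rounding up, as the tables do now:

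| Table and alpha | Sizes at 40:60 |
|---|---|
| Table 1, 0.05 (HR 0.8, 0.9, 1.0) | 103, 165, 285 |
| Table 1, 0.10 | 75, 121, 208 |
| Table 2, 0.025 (HR 0.4 to 0.8) | 49, 86, 157, 322, 821 |
| Table 2, 0.05 | 39, 68, 124, 254, 647 |
| Table 2, 0.10 | 28, 49, 90, 185, 472 |

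Table 1 then agrees with the text at 165. The cost is protocol wording only: no extra patients and no change to the analysis. The stated superiority power becomes less favourable.

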## 5. TREATMENT OF SUBJECTS

### 5.1 Treatment Protocol

Radiotherapy will be planned and delivered in every center according to the treatment protocol (Appendix 1).

### 5.2 Experimental treatment arm (arm 1)

Since prospective phase III research on the optimal fractionation regimen is sparse, a radiobiological theoretical optimal regimen is chosen from retrospective studies and phase I/II studies. The linear-quadratic model describes cell killing, both for tumor control and for normal tissue complications following exposure to a varying amount of radiation. The most modern method of comparing fractionation schedules is to use the linear quadratic equation to calculate the equivalent dose in 2 Gy fractions (EQD2). For  $PTV_{boost}$ , the EQD2 may be up to 40 Gy based on the maximal cumulative dose of 100 Gy advised by Sminia and Mayer [32, 33]. For this reason, the dose on PTV was selected to be 4 fractions of 5.5 Gy ( $EQD2_{\alpha/\beta=2} = 41$  Gy).

For PTV, the maximal dose should not exceed 8 fractions of 5 Gy ( $EQD2_{\alpha/\beta=2} = 70$  Gy). In a prospective phase I trial, hypofractionated stereotactic radiotherapy was given using 5 Gy per fraction to doses ranging from 20 to 50 Gy on a dose escalation program, in patients with recurrent glioma with a median target volume of 24cc. Exceeding 8 fractions of 5 Gy resulted in 6.4 times more radiation damage [26]. Four fractions of 7.5 were considered safe with a comparable  $EQD2_{\alpha/\beta=2}$  of 71 Gy.

Experimental treatment schedule will be 4 fractions of 7.5 Gy SIB to the CE on CE-T1 and 4 fractions of 5.5 Gy to the CE with a 10mm margin.

### 5.3 Standard treatment arm (historic controls, arm 2)

In 1999, a phase I dose escalation of hypofractionated stereotactic radiotherapy in recurrent or persistent malignant gliomas was conducted. Three different total dose levels were sequentially evaluated: 24.0 Gy in 3.0 Gy fractions (five lesions), 30.0 Gy in 3.0 Gy fractions (10 lesions), and 35.0 Gy in 3.5 Gy fractions (nine lesions). No grade 3 toxicities were observed and the response rate was 78% [34]. From that time, 10 fractions of 3.5 Gy is a generally accepted regimen. Until now, this schedule has shown to be safe and effective in practice [35].  $EQD2_{\alpha/\beta=2}$  of this schedule is 48 Gy.

### 5.4 Use of co-intervention

Concomitant dexamethasone and anticonvulsant therapy is allowed. Salvage surgery prior to start radiation is allowed. Systemic therapy including chemotherapy, immunotherapy or targeted therapy during ReRT is not allowed.

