## 4. STUDY POPULATION

### 4.1 Population

Patient enrollment in the experimental arm (arm 1) continues until 66 adult patients with recurrent gliomas eligible for re-irradiation are recruited **in total** (RISING A & B) in the participating hospitals. The recruitment period will be approximately 30 months with an active follow-up time of 12 months.

The control group of the original RISinG study (A) had 16 patients. An additional 83 patients will be selected from the retro-RISING study, a multicenter retrospective nation-wide population-based cohort study, in which details of patient-, tumor- and treatment –related data of patients with a recurrence of a primary brain tumor since January 2002 up to December 2022 in the Netherlands will be collected for arm 2. Out of the retro-RISING trial, we will select only the patients with a treatment schedule of 10x3.5Gy. These patients will be individually matched to the patients in the experimental arm.

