### 4.2 Inclusion criteria

In order to be eligible to participate in study arm 1 and 2, a subject must meet all of the following criteria:

- Supratentorial recurrent high-grade glioma with contrast enhancement on CE-T1.
- The gold standard is histological evidence of a recurrence. When a surgical procedure to acquire this evidence is not desirable or possible, a recurrence may be diagnosed by radiological imaging alone, taking the following in consideration:
  - Agreement of the tumor board or a consultant neuro-radiologist that imaging changes are in keeping with recurrence.
  - An interval of no less than 3 months since last (chemo)radiotherapy.

- Utilization of the RANO criteria for tumor progression [29].
- If needed, additional imaging sequences such as PET and perfusion MRI.
- Unifocal glioma (i.e. lesions clustering around residual surgical cavity).
- Prior course of treatment including radiotherapy with an EQD2 ( $\alpha/\beta = 2$ ) of at least 47Gy.
- Age  $\geq 18$  years.
- Karnofsky Performance Score 60 or above.
- Ability of subject to understand character and individual consequences of the clinical trial (arm 1).
- Patients who received re-irradiation for the recurrence of a primary brain tumor with a treatment schedule of 10x3.5Gy (arm 2).

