### 4.3 Exclusion criteria

A potential subject who meets any of the following criteria will be excluded from participation in this study (arm 1 and 2):

- Previous re-irradiation or prior radiosurgery or prior treatment with interstitial radioactive seeds.
- CE-T1 tumor diameter greater than 6cm ( reflecting a spherical tumor of 125cc).
- Time interval of less than 6 months after prior radiotherapy.
- Time interval of less than 3 weeks after last re-resection (1 week for biopsy).
- Known carcinoma < 3 years ago (excluding Carcinoma in situ of the cervix, basal cell carcinoma, squamous cell carcinoma of the skin) requiring immediate treatment interfering with study therapy.
- Women with childbearing potential without adequate contraception.

If a patient is not eligible for arm 1 based on the MRI results (e.g. T1-CE diameter >6 cm, reflecting a spherical tumor of 125 cc), these non-eligible patients are being replaced by new patients. These non-eligible patients are not included in the statistical analysis of the trial and treated with the physicians' choice.

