#### 6.1.2 Secondary study parameters/endpoints

The key secondary endpoint is:

- Progression free survival (PFS) counted from the first date of re-irradiation until the date of MRI evidence of tumor recurrence or death due to any cause. Agreement of the tumor board or a consultant neuro-radiologist that imaging changes are in keeping with recurrence and not radionecrosis is necessary.

Other secondary endpoints include the following:

- Recurrence Patterns on MRI.
- Radiation toxicity graded by CTCAE v5.0
- Anti-edema therapy (including Dexamethasone and Bevacizumab use).
- Health Related Quality of Life (HRQoL) prospectively monitored by EQ-5D-5L, EORTC QLQ-C15-PAL and EORTC-QLQ-BN20+2 questionnaires. (only for the experimental arm 1, cannot be analyzed retrospectively in the control arm 2).

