#### 8.1.1 OS and PFS

All statistical tests for the efficacy endpoint OS and PFS will be performed according to intention-to-treat (ITT) principle, which is the most unbiased method. Considering the trial being a non-inferiority trial, which is more sensitive to bias, a secondary per-protocol (PP) analysis will be done for OS [43]. The PP analyses will be performed on a “subset of patients who complied sufficiently with the protocol, such as exposure to treatment, availability of measures and absence of major protocol violations” according to the ICH E9 guidelines. The ITT analysis includes all participants. Start date of ReRT will be used as time is 0. Patients not known to have died during the study will be censored for OS at the day they were last known to be alive. Patients free from progression and alive at the last visit will be censored for PFS at the day of last assessment. Endpoints are measured from the first date of re-irradiation.

Distributions of OS and PFS will be estimated by the Kaplan-Meier method. The OS rates at one year, PFS rates at six months and medians of OS and PFS will be presented with two-sided 95% confidence interval(CI) computed using the log-log transformation.

To minimize the effect of confounding when estimating the difference between the treatment and retrospective control group, stabilized inverse probability of treatment weighting (SIPTW) using propensity scores will be applied when comparing the groups on OS and PFS.

Propensity scores will be estimated using logistic regression including important covariates for OS and PFS: primary histology, GTV, KPS and age.

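### The ban on systemic therapy during re-irradiation is not carried over to the 83 registry controls, who can therefore differ from arm 1 in co-treatment

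*Protocol*

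**What the plan says.** Section 5.4 (Use of co-intervention) reads: "Systemic therapy including chemotherapy, immunotherapy or targeted therapy during ReRT is not allowed". The sentence names no arm. It follows the sections on the experimental arm (5.2) and the historic controls (5.3).

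Arm 2 has 99 patients: 16 from the control arm of RISING trial A and 83 from the retro-RISinG registry, which covers January 2002 to December 2022 (section 4.1). The rules that shape the registry part are:

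- **Selection (4.1):** "Out of the retro-RISING trial, we will select only the patients with a treatment schedule of 10x3.5Gy".
- **Inclusion (4.2):** "In order to be eligible to participate in study arm 1 and 2, a subject must meet all of the following criteria". The list includes one line specific to arm 2, on the 10 x 3.5 Gy schedule, and none on concurrent systemic therapy.
- **Exclusion (4.3):** also headed as covering both arms. No line concerns systemic therapy.
- **Matching (3):** "This control group will be matched to the patients in the experimental arm on an individual level for" age, gender, WHO grade of the primary tumour, interval between the two radiation courses, and MGMT status.
- **Weighting (8.1.1):** "Propensity scores will be estimated using logistic regression including important covariates for OS and PFS: primary histology, GTV, KPS and age".

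Section 6.1.2 lists as a secondary endpoint "Anti-edema therapy (including Dexamethasone and Bevacizumab use"), so bevacizumab appears there as anti-edema treatment, with no statement of when it may be given.

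**The concern.** A rule that something is not allowed governs patients still to be treated. It cannot act on treatment that registry patients have already received. It reaches them only if it is written as a criterion for choosing controls, and it is not. Followed as written, the protocol admits a registry patient who had 10 x 3.5 Gy with concurrent chemotherapy, while an arm 1 patient given the same would be a protocol violation.

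The trial asks whether 4 fractions are non-inferior to 10. If part of the comparator also received systemic therapy during re-irradiation, the contrast mixes fractionation with co-treatment. A drug benefit among controls would make the experimental regimen look worse and cost power. If concurrent drugs were given mainly to patients with a worse outlook, the controls would look worse and non-inferiority would be too easy to show. Concurrent bevacizumab could also bear on PFS and on the anti-edema endpoint.

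**Working it through.** **Step 1: does any rule screen for concurrent systemic therapy in arm 2?**

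| Rule | Section | Addresses it? |
|---|---|---|
| Registry selection | 4.1 | No |
| Inclusion, arms 1 and 2 | 4.2 | No |
| Exclusion, arms 1 and 2 | 4.3 | No |
| Five matching factors | 3 | No |
| Four propensity covariates | 8.1.1 | No |

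**Step 2: reproduce the planned sample size (4.4).** Inputs: one-sided alpha 0.05, power 0.80, margin 1.4, true HR 0.90, allocation 40:60, event proportion 0.8.

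Events = (1.645 + 0.842)² / (0.4 × 0.6 × [ln(1.4/0.9)]²) = 131.96, so 132. N = 131.96 / 0.8 = 164.95, so 165. This matches the stated 165 (99 + 66). Power with 132 events is 80.0%.

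**Step 3: illustrate the effect of exposure.** Two inputs are assumptions, because the documents give neither: f, the share of the 83 registry controls exposed, and h, the death hazard ratio of exposed against unexposed controls. The 16 trial A controls are taken as unexposed.

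- Registry share of controls: 83/99 = 0.838.
- Control hazard multiplier (log-average approximation): m = h^(0.838 f).
- Expected HR = true HR / m.
- Probability of declaring non-inferiority = Φ(√(132 × 0.24) × ln(1.4/expected HR) − 1.645), where √(132 × 0.24) = 5.63.

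Worked case, f = 0.3 and h = 0.70: m = exp(0.838 × 0.3 × ln 0.70) = exp(−0.0897) = 0.914. Expected HR = 0.90/0.914 = 0.984. Φ(5.63 × ln(1.4/0.984) − 1.645) = Φ(0.34) = 63%.

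*Drugs lower the control hazard, true HR 0.90:*

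| f | h | Expected HR | Power |
|---|---|---|---|
| 0% | – | 0.900 | 80% |
| 10% | 0.85 | 0.912 | 78% |
| 10% | 0.70 | 0.927 | 75% |
| 30% | 0.85 | 0.938 | 73% |
| 30% | 0.70 | 0.984 | 63% |

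*Exposed controls do worse through selection, true HR 1.4 (the margin), h = 1.25:*

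| f | Expected HR | One-sided type I error |
|---|---|---|
| 0% | 1.400 | 5.0% |
| 10% | 1.374 | 6.2% |
| 30% | 1.324 | 9.2% |

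**The case against.** Section 5.4 names no arm, and elsewhere the protocol often marks what is for arm 1 only, so 5.4 may be meant for both. Section 8.1.1 also plans a per-protocol OS analysis restricted to patients without major violations. Detailed control selection may sit in the registry study's own protocol, which is not shown. These points stand as far as intent goes. They do not repair the text: if both arms were meant, the arm 2 criteria omit the rule, and the per-protocol analysis is secondary and covers OS only.

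It can also be said that matching or weighting could not balance a co-treatment that is barred in arm 1. That is right. It is why the remedy belongs in the selection of controls rather than in the propensity model.

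The figures deserve caution. Neither f nor h comes from the documents, and h is applied to all of follow-up although re-irradiation lasts only 2 to 3 weeks.

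A reader might infer more than the documents support:

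- *That controls are chosen on the schedule alone.* They are not. The eligibility lists in 4.2 and 4.3 and five matching factors also apply.
- *That exposed patients are in the comparator.* The documents only leave this possible; they report no exposure.
- *That all 99 controls are affected.* Only the 83 registry patients clearly are. The text of trial A is not shown.
- *That the comparison is 4 fractions alone against 10 with drugs.* Section 5.4 concerns only the re-irradiation period and restricts nothing afterwards in either arm.

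**Conclusion.** The point holds in this form: the protocol bans a co-treatment but gives no rule that keeps it out of, or accounts for it in, the 83 registry controls, who make up 84% of arm 2. The primary OS comparison and PFS may be biased in a direction that cannot be known from the documents. Under the assumptions above, the cost is between 2 and 17 percentage points of power, or a rise in one-sided type I error from 5% to between 6% and 9%. These ranges illustrate sensitivity; they do not estimate the bias. If no registry patient on this schedule had concurrent systemic therapy, the effect is nil. Who qualifies as a control is a matter of eligibility, which this protocol fixes itself, so it is more than detail left to an analysis plan.

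**What to change.** 1. State in 4.2 or 4.3 that the 5.4 restriction also applies to arm 2 as a selection criterion: no systemic anticancer therapy given or planned concurrently with re-irradiation.
2. Apply it to the registry before any outcome is viewed.
3. Report a sensitivity analysis that adds the exposed controls back.
4. Reconcile 5.4, which bars targeted therapy during re-irradiation, with 6.1.2, which records bevacizumab as anti-edema therapy. Which reading is right is for the sponsor to settle; the same one must hold in both arms.

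One caution on wording. Excluding controls for what was given after the first fraction conditions on events after time zero, while an arm 1 patient with the same exposure stays in the intention-to-treat set. Where the registry permits, the criterion should rest on what was planned at the start of re-irradiation.

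The cost is one line of text, a smaller control pool, and reliance on the registry recording the timing of systemic therapy, which the protocol does not confirm. The planned N stays at 165 as long as 83 eligible registry controls remain.
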